**Household WASH, environmental health and food safety evaluations**

Each recruited household will be asked to engage with a range of qualitative and quantitative data collection methods to gain an understanding of the contextual and psychosocial elements of their household, individual and habitual WASH practices as outlined in IBM-WASH
^
33
^. Questions will be asked of household members at the baseline assessment (combined with the household and individual CRFs), and a checklist and sanitation inspection form will be completed by a member of the study team at each visit to evaluate WASH infrastructure. Lastly, a household plan will be completed at baseline to contextualise the household infrastructure where specific activities take place (including perceived high-risk areas) and aid in analysis.

WASH practices will be assessed via checklist and structured observations at households and identified for “intensive surveillance”, at both the baseline and fourth visit. Observations will be undertaken on 3 consecutive days, for a period of 6 hours per day, with two morning sessions (6am-12pm) and one afternoon session (12pm-6pm) to describe WASH practice over the period of a day. The focus on early sessions has been chosen due to previous studies illustrating that key WASH activities occurred mainly in the mornings
^
34
^. Observations will be recorded by research staff and summarised in a structured format for content analysis to enable the identification of critical control points around WASH behaviours for faecal and environmental exposure.

**Understanding WASH behavioural drivers**

Psychosocial drivers of WASH practices will be explored using the Risks, Attitudes, Norms, Abilities and Self-Regulation (RANAS) Model, undertaken at up to 100 households in each region
^
35,
36
^. The RANAS questionnaire design will be informed by the structured observations in intensive households and focus on hand hygiene, food preparation, waste management, water usage and environmental exposure. The RANAS survey will be conducted with 2 household members in each household, and where possible, will be directed to the household head (e.g. father) and one household worker (household staff member). RANAS data will be analysed using an ANOVA mean comparison to determine the differences between doer and non-doer contextual and psychosocial factors for potential targeted behaviours. The data from this survey will be used to inform potential behaviour change techniques which could be used to tackle high risk transmission areas identified in the agent-based model.

**
*Assessment of broader environmental exposure*
**

Transect walks of each region will be undertaken using an integrated approach to the collection and evaluation of environmental, WASH and microbiological data to understand the wider context in which household members are living. Based on the principles of the
SaniPath method, walks will be undertaken with community leaders using walking interviews, while collecting video footage and photographs and geolocating walk routes and sampling sites. Reference will be made to specific Shit Flow Diagrams (SFD), where available, which visually describe excreta flow in urban and rural settings, and data will be mapped to provide a spatial outline of potential pathways for faecal exposure
^
37–
39
^. Wherever feasible, longitudinal data will be collected on study sites to assess the effects of seasonality. This novel adaption of the SaniPath tool will enable us to integrate environmental AMR data into urban and rural WASH exposure pathways.

Observations and structured checklists will be completed at 10 public and institutional settings within each of the five sites (n=50). This will be complemented by Focus Group Discussions (FGDs) and In-depth interviews (IDIs) with key informants (heads of household, primary caregivers, school children, market vendors, etc.) to explore perceptions of barriers and challenges to WASH posed by circumstances of daily life.

**
*Spatial analysis and integration of datasets into an agent-based model*
**

The initial approach will be to determine variables that have strong associations with ESBL status using model-based statistical analysis
^
40
^. Spatial and temporal correlations will be accounted for using both geostatistical and agent-based modelling techniques to increase the precision of our inference, and hence insight into the main demographic and environmental drivers of transmission and carriage. Geostatistical models will initially be used as a phenomenological way of detecting such associations in the quantitative elements of our data
^
41
^. Findings from our qualitative components will then be used to inform the structure of an agent-based model. This will allow us to test different systems models of social and behavioural features of the population that may contribute to ESBL emergence, transmission, and colonisation/decolonisation of individuals
^
41
^.

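### RANAS respondents are preferred by household role, not by responsibility for the behaviour surveyed, so for task-specific behaviours doer status may be confounded with role

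*Protocol article*

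**What the plan says.** All of the RANAS text is in the protocol article, section Understanding WASH behavioural drivers.

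- Scale: the survey is "undertaken at up to 100 households in each region".
- Respondents: "The RANAS survey will be conducted with 2 household members in each household, and where possible", it "will be directed to the household head (e.g. father) and one household worker (household staff member").
- Behaviours: the questionnaire is to "focus on hand hygiene, food preparation, waste management, water usage and environmental exposure".
- Analysis: an "ANOVA mean comparison to determine the differences between doer and non-doer contextual and psychosocial factors for potential targeted behaviours".
- Use: the data will be "used to inform potential behaviour change techniques which could be used to tackle high risk transmission areas" that the agent-based model identifies.
- Link to the observations: "The RANAS questionnaire design will be informed by the structured observations in intensive households". This concerns what is asked, not who is asked.

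The next section, Assessment of broader environmental exposure, plans group discussions and interviews with "key informants (heads of household, primary caregivers, school children, market vendors, etc".). Heads and primary caregivers are listed there as separate groups. Study status reports that the RANAS questionnaires have been undertaken.

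**The concern.** A doer/non-doer comparison is informative when both groups face the same task and differ in whether they follow the target practice. Differences in beliefs, norms or perceived ability can then be read as possible drivers. If one group consists largely of people to whom the task does not fall, the same differences may only reflect who those people are.

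The preferred pair is a head, with a father as the example, and a staff member. These two groups are likely to differ in status, and possibly in sex and age. Food preparation, waste handling and water handling usually fall to particular people. At stake is the survey's stated purpose: a factor that separates heads from workers could be taken for one that separates good from poor practice, and a behaviour change technique chosen on that basis.

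**Working it through.** The article gives no sample-size reasoning, error rate or effect size for this survey, so there is no planned figure to reproduce. The check is of the text, with a simple count and a bound.

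**1. Is any respondent tied to a behaviour?** The selection sentence names two roles. Neither is defined by performing, or being responsible for, any of the five behaviours. The primary caregiver and the main food or water handler are not named. They are reached only if they happen to be the head, the worker or a substitute. The article names no substitute for a household without staff.

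**2. Does the analysis bring role in?** The described method is a comparison of means between doers and non-doers. No role term, stratification or restriction to responsible respondents is mentioned.

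**3. What does that do to the comparison?** Suppose that workers score d points above heads on some item, and that within each role the item is unrelated to the behaviour. Let a be the share of heads among doers and b the share of heads among non-doers. With M the mean among workers:

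- mean among doers = M − a·d
- mean among non-doers = M − b·d
- doer minus non-doer = d·(b − a)

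If heads are equally common in both groups (a = b), the spurious difference is 0. If all doers are workers and all non-doers are heads (a = 0, b = 1), it is the full d. The article gives none of d, a or b, so the bias lies between nothing and the whole role difference.

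**4. Which behaviours are exposed?** Food preparation, waste management and water usage are tasks that can be assigned to one person. Hand hygiene and environmental exposure concern each individual, so a head is a valid respondent for them.

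**5. How many respondents perform a given task?** Two respondents in up to 100 households give up to 2 × 100 = 200 per region, of whom up to 100 are heads if the preference is met everywhere. Beyond this the document is silent, so the following rests on assumptions only: 10–30% of heads perform the task, 10–30% of households have staff, and all staff perform it. Let p be the share of substitutes, in households without staff, who perform it. Per 100 households:

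- low end: 10 heads + 10 staff + 90p
- high end: 30 heads + 30 staff + 70p

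At p = 0 this gives 20 to 60 of 200. At p = 1 it gives 110 to 130 of 200. The respondent rule does not settle whether performers are a minority or a majority.

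**The case against.** A reader might infer that the survey measures drivers in the wrong people and leaves the real performers unmeasured. The document does not support that.

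- The rule is a preference, qualified by where possible. The only firm requirement is two members per household, so a caregiver or food preparer is not excluded.
- The household worker may well be the person who does these tasks.
- Non-doers are needed for the comparison, and a head's norms and decisions can matter as context. The difficulty arises only when a non-doer is someone to whom the task does not fall.
- Performers are also covered elsewhere: by three days of structured observation in intensive households, by individual hand-washing data (Table 1), and by discussions and interviews that name primary caregivers. These do not supply RANAS scores, but performers are not ignored.
- A figure of 20 to 60 performers out of 200 would be the worst case on unsourced inputs, as step 5 of the working shows.
- How a doer is defined, who substitutes for an absent staff member, and how a respondent without the task is handled may stand in the questionnaire or full protocol, which are not shown. Their absence from an article is not a fault.

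All of this stands, and it limits the point. It does not remove it. What the article does state is a selection preference by role and a comparison by behaviour, with nothing connecting the two.

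**Conclusion.** The point holds in a limited form. Respondents are not matched to the behaviour surveyed, so for food preparation, waste management and water usage doer status may be confounded with household role. Hand hygiene and environmental exposure are less affected. The size cannot be computed: it depends on how tasks are divided, how many households have staff, who substitutes, and how far heads and workers differ on each item, and the document gives none of these. The conclusion also assumes that the full analysis is the unadjusted comparison that the article describes.

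Severity is minor. The survey explores drivers and informs the choice of techniques. The study's aim, ESBL risk factors and transmission at household level, does not rest on this comparison, and the ESBL estimates are unaffected.

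**What to change.** For the data already collected:

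- Run each task-specific comparison only among respondents responsible for that task. Define doer and non-doer by whether they follow the target practice, not by whether they perform the task at all. Restricting to people who report performing the task, without that redefinition, could leave no non-doers.
- Adjust for, or stratify by, respondent role and sex.
- Tabulate role by behaviour and doer status, so that readers can see how far the two overlap.
- Where few responsible respondents remain, say so and present the result as descriptive.

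This assumes that role, sex and task responsibility can be recovered. Data management and analysis plans to link RANAS data to the other study records, and Table 1 lists participant demographics and information on the head, which should help with role and sex. If task responsibility was not recorded, report that as a limitation.

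For any further RANAS round, keep the head and make the second respondent the member mainly responsible for the behaviour, paid or unpaid. The number of interviews stays the same.

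The cost is some extra analysis and smaller samples in some behaviour-specific comparisons.

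### The RANAS survey takes two respondents per household, but the stated doer/non-doer ANOVA has no household term, so its standard errors do not reflect the pairing

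*Protocol article*

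**What the plan says.** Everything on RANAS sampling and analysis is in one paragraph of the protocol article, under the heading Understanding WASH behavioural drivers.

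- Size: the survey is "undertaken at up to 100 households in each region".
- Respondents: "The RANAS survey will be conducted with 2 household members in each household, and where possible, will be directed to the household head". The second intended respondent is a household worker, under the same qualification.
- Analysis: "RANAS data will be analysed using an ANOVA mean comparison to determine the differences between doer and non-doer contextual and psychosocial factors". No household, role or site term is named, and no robust variance.
- Use: "The data from this survey will be used to inform potential behaviour change techniques".

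The article does address correlation under its next heading, on spatial analysis and the agent-based model: "Spatial and temporal correlations will be accounted for using both geostatistical and agent-based modelling techniques". That sentence concerns variables associated with ESBL status. Nothing links it to the RANAS comparison.

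**The concern.** Two people in one household share water, sanitation, kitchen and much of their social setting, so their scores on the contextual and psychosocial factors are likely to be correlated. A comparison of doer and non-doer means with no household term takes its standard error from all respondents as if each were a separate unit. That holds only if scores, or doer status, are uncorrelated within households.

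There is a second, more conditional issue. The survey aims at two different kinds of respondent. If heads and workers differ both in how often they perform a behaviour and in how they score, the doer/non-doer contrast partly carries a head/worker contrast.

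What is at stake is which factors appear to separate doers from non-doers, and with what precision, when the results are used to suggest behaviour change techniques.

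**Working it through.** The document gives no significance level, standard deviation, within-household correlation or doer share for RANAS, so there is no stated figure to reproduce.

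**Inputs.** From the document: cluster size m = 2, and up to 100 households, hence up to 200 respondents per region. Assumed: two-sided 5% test, within-household score correlation ρ of 0.2, 0.4 and 0.6, and three patterns of doer status within households.

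**Clustering.** The variance of the difference in means is multiplied, relative to what the ANOVA assumes, by about

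DE = 1 + (m − 1) × ρ(score) × ρ(doer) = 1 + ρ(score) × ρ(doer),

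and the actual type I error is 2 × [1 − Φ(1.96/√DE)]. To this approximation the number of households does not matter.

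*Both members share doer status, ρ(doer) = 1:*

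| ρ(score) | DE | True SE / assumed SE | Effective N of 200 | Actual error |
|---|---|---|---|---|
| 0.2 | 1.2 | 1.10 | 167 | 7.4% |
| 0.4 | 1.4 | 1.18 | 143 | 9.8% |
| 0.6 | 1.6 | 1.26 | 125 | 12.1% |

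Simulation with 100 pairs gave 7.5%, 9.2% and 12.4%.

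*Status unrelated within households, ρ(doer) = 0:* DE = 1 and the error is 5%. Simulation at ρ(score) = 0.1, 0.3 and 0.5 gave 5.4%, 4.7% and 5.3%.

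*Members always differ, ρ(doer) = −1:* DE = 0.8, 0.6 and 0.4. Simulation gave 3.1%, 1.3% and 0.2%. The test is conservative and loses power.

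**Bias from clustering alone.** With a true difference of zero, the mean simulated difference stayed within about 0.002 SD of zero in every pattern. Pairing affects the standard error, not the estimate.

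**Role.** If the true doer effect is zero, the size of the difference due to role is

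(role difference in score) × |share of workers among doers − share of workers among non-doers|.

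All values below are assumed:

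- Doers are 50% of heads and 50% of workers: the shares are equal, so the difference is 0 whatever the role gap.
- Doers are 40% of heads and 60% of workers, role gap 0.5 SD: 0.5 × (0.60 − 0.40) = 0.10 SD.
- Doers are 30% of heads and 70% of workers, role gap 0.5 SD: 0.5 × (0.70 − 0.30) = 0.20 SD.
- Doers are 30% of heads and 80% of workers, role gap 0.3 SD: 0.3 × (0.8/1.1 − 0.2/0.9) = 0.3 × (0.727 − 0.222) = 0.15 SD.

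**The two effects are not additive.** In the last example, if status is otherwise independent within pairs, the doer correlation is (0.25 × −0.25)/(0.55 × 0.45) = −0.0625/0.2475 = −0.25. At ρ(score) = 0.3, DE = 1 − 0.3 × 0.25 = 0.92, which is slightly conservative. The 7% to 12% error rates belong to households whose members share status, and a strong role split works against that.

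**The case against.** The strongest reply is that the criticism reads too much into one sentence of a condensed article. The text does not say that respondents are treated as independent or that role is disregarded. ANOVA as a family can include a household block and a role factor, and such terms are often left to a fuller plan. This has weight as to intent. It does not settle the matter, because the article itself fixes paired sampling and then names a comparison of means between two groups. That comparison, carried out as described, has no place for the household.

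Four further points stand and limit the finding:

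- A reader might infer that the p-values and mean differences are simply wrong. The document does not support that. Error rates can be too high, about right or too low, and clustering alone leaves the means unbiased.
- A reader might take the head and worker roles as fixed by design. Only the count of two is. The roles are targeted where possible.
- Confounding by role rests on assumed values. The unadjusted difference is also a true description of doers and non-doers, so adjusting for role changes the question and should not silently replace the unadjusted result.
- RANAS is exploratory and feeds possible techniques. No RANAS significance rule or sample-size figure is stated that could be shown to be wrong, and the ESBL analyses are separate.

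**Conclusion.** The point holds in a limited form. The stated analysis does not match the paired sample, and followed as written its standard errors are miscalibrated whenever both scores and doer status are correlated within households. The size is an actual error of about 7% to 12% for a nominal 5% test with shared status, about 5% with unrelated status, and about 0.2% to 3% with opposite status. This assumes score correlations of 0.2 to 0.6. Real households will probably lie between these extremes.

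A role-related shift of 0 to about 0.20 SD is possible under the values tried, but nothing in the document shows that it will occur. Severity is moderate to low: the analysis supports the main ESBL work and does not decide it.

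**What to change.** Analyse each RANAS factor with a linear mixed model that has doer status and site as fixed effects and a household random intercept. Household-clustered standard errors with the same fixed effects would also do. Report mean differences with 95% confidence intervals. This is valid whether members share doer status, differ or are unrelated in it.

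Beside that, report the same contrast adjusted for the respondent's actual role, since the intended head/worker split will not always be achieved. Present the two together so that readers can see how much of the difference goes with role.

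The cost is analysis wording and a small amount of extra work. The Study status section says the questionnaires are complete, and the data management section plans record linkage with RANAS, so no new data should be needed provided household and role identifiers were kept. Where members share doer status, the intervals will be wider, as they should be.

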### Data collection

**
*Case Report Forms (CRFs)*
**

Study CRFs have been designed by an interdisciplinary working group of the DRUM consortium that included specialists in human health, animal health, food, water and environmental microbiology, WASH & Environmental health and medical anthropology. Questions were selected from pre-tested tools evaluating regional demographics, human and animal health, WASH infrastructure and behavioural practices, humans and animal ABU determinants and environmental exposures
^
29,
30
^. These questions were inputted into CRFs that were tailored to the resident population, structured into either individual or household level, thematically separated into key drivers of AMR and translated into local languages (
Table 1).

**Table 1. T1:** DRUM CRF themes and data capture.

	Individual Level Data	Household Level Data
**Demographic**	· Participant Demographics	· Household Demographics · Socio-Economic Information · Household Head Information
**Health**	· Health Status and Comorbidities · Regular Medication Use · Recent Illness	· Household Health Seeking Behaviour
**Exposure Risk**	· Healthcare Exposure · Travel and Residency · Health Seeking Behaviour	· Visitors into the household
**Antibiotic Usage**	· Antibiotic Usage	· Household Experience of Illness and Antibiotics
**WASH**	· Hand-Washing Data	· Household WASH Infrastructure · Toileting Behaviour · Waste Management · Water Usage and Management · Washing and Bathing Practices · Food Preparation and Hygiene Information. · Hand-Washing Data
**Environmental**		· Household Infrastructure · Household Environment
**Animal**		· Household Animal Husbandry · Animal Health and Disease Prevention · Drug Usage in Household Animals (including antibiotics)

At the baseline visit, these CRFs will be completed to provide information at the individual and household level on human health, ABU, socioeconomic status, health seeking behaviour, structural and behavioural WASH practices and animal husbandry (Extended data). At each follow-up visit, changes to human health, household practices and antibiotic exposure will be assessed (Extended data).

**
*Longitudinal microbiological sampling*
**

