### Data management and analysis

In Uganda CRF data and laboratory data will be collected using REDCap (version 10.0.25). In Malawi CRF data will be collected using tablets with Open Data Kit software (ODK, 1.4.10) and laboratory data will be collected using Teleform Data Capture software (10.7). Initial transcription (where needed) and data cleaning will be performed within the local data centres in Uganda and Malawi, close to the data collection context. These data will then be pulled nightly from the local data centres to the University of Lancaster (UoL), UK and formalised into an SQL database to facilitate full record linking with RANAS and WASH study data, extract query construction, and final quality assurance (
Figure 5). All data will be securely stored with restricted access to the study PIs and database administrators at Malawi-Liverpool Wellcome Trust (MLW, Malawi), IDI (Infectious Diseases Institute, Uganda) and Lancaster, and shared where required with specific members of the DRUM project team using a secured instance of Dataverse hosted on UoL servers.

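### The named RANAS analysis, an unadjusted ANOVA of doers against non-doers, cannot show whether a psychosocial difference remains at equal access to water, soap or a latrine

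*Protocol article*

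**What the plan says.** Under *Understanding WASH behavioural drivers*, the protocol article states the aim: "Psychosocial drivers of WASH practices will be explored using the Risks, Attitudes, Norms, Abilities and Self-Regulation (RANAS) Model". The survey is "undertaken at up to 100 households in each region", and "The RANAS survey will be conducted with 2 household members in each household". One analysis is named: "RANAS data will be analysed using an ANOVA mean comparison to determine the differences between doer and non-doer contextual and psychosocial factors". On use, "The data from this survey will be used to inform potential behaviour change techniques", applied to high-risk areas that the agent-based model identifies.

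Three other places bear on the point.

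- Table 1 (*Data collection*) lists "Household WASH Infrastructure" and socio-economic information among the household-level data. Under *Household WASH, environmental health and food safety evaluations*, "a checklist and sanitation inspection form will be completed by a member of the study team at each visit to evaluate WASH infrastructure".
- *Data management and analysis* describes a database built "to facilitate full record linking with RANAS and WASH study data".
- The model-based analysis under *Spatial analysis and integration of datasets into an agent-based model* has ESBL status as its outcome. Nothing there extends it to doer status.

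**The concern.** In the named analysis, contextual factors stand on the same side as the psychosocial ones: both are quantities whose means are compared between doers and non-doers. Neither is a covariate, and a comparison of this kind holds nothing constant.

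Someone with a tap or a latrine is more likely to be a doer. The same person may also report higher perceived ability or stronger norms, because the behaviour is easier where the infrastructure exists. A psychosocial difference can then appear although, among people with equal access, the psychosocial score has no relation to the behaviour. Site could act in the same way if sites are pooled, since *Site selection* says the settings were chosen to give variation in WASH behaviours.

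The stated interest is in psychosocial drivers, and the results are to inform behaviour change techniques. For that purpose it matters whether the barrier is psychological or structural, and the named comparison cannot separate the two.

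**Working it through.** **The plan's own figure.** There is none to reproduce. The article gives no alpha, effect size, SD or power for the RANAS survey.

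**Input from the document.** Up to 100 households per region, 2 respondents each: 100 × 2 = 200 respondents. The article does not define a region here. The 200 is a ceiling for one region, without pooling.

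**Assumed inputs (none is in the document).** Infrastructure is present for 50%. Without it, the probability of being a doer is 0.30. With it, the odds of doing are multiplied by OR = 3 or 6. The psychosocial score has SD 1 within infrastructure level and is higher by d = 0.3, 0.5 or 0.8 where infrastructure is present. Given infrastructure, score and behaviour are unrelated. The test is two-sided at 5%.

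**Step 1: probability of doing with infrastructure.** The odds without are 0.30/0.70 = 0.4286.

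- OR 3: odds 1.286, probability 1.286/2.286 = 0.5625.
- OR 6: odds 2.571, probability 2.571/3.571 = 0.72.

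**Step 2: share with infrastructure in each group.** With a 50:50 split the halves cancel.

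- OR 3: doers 0.5625/(0.5625 + 0.30) = 0.652; non-doers 0.4375/(0.4375 + 0.70) = 0.385; gap 0.268.
- OR 6: doers 0.72/(0.72 + 0.30) = 0.706; non-doers 0.28/(0.28 + 0.70) = 0.286; gap 0.420.

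**Step 3: spurious difference in the score** = d × gap.

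- OR 3, d 0.3: 0.3 × 0.268 = 0.08 SD.
- OR 6, d 0.5: 0.5 × 0.420 = 0.21 SD.
- OR 6, d 0.8: 0.8 × 0.420 = 0.34 SD.

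**Step 4: how often a 5% test flags it at 200 respondents.** Worked for OR 6, d 0.5: about 102 doers and 98 non-doers. The within-group SD is √(1 + 0.25 × 0.206) = 1.025, where 0.206 is the average of share × (1 − share) in the two groups. The standard error is 1.025 × √(1/102 + 1/98) = 0.145, and 0.21/0.145 = 1.45. The chance of exceeding 1.96 is then about 30%. Simulation gives:

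| Assumed OR, d | Unadjusted ANOVA | Adjusted for infrastructure |
|---|---|---|
| 3, 0.3 | about 8% | about 5% |
| 6, 0.5 | about 30% | about 5% |
| 6, 0.8 | about 60% | about 5% |

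Repeating this with infrastructure shared by both members of a household changes little (about 8%, 30% and 60% unadjusted).

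**Step 5: a second set of assumptions.** Infrastructure again at 50%, with P(doer) with and without it running from 0.6/0.4 to 0.8/0.2, and d from 0.25 to 0.8. At 200 respondents the unadjusted rate runs from about 5% to 88%. In the middle case (0.7/0.3, d 0.5) it is 28% unadjusted and 4.6% adjusted; with only 100 respondents it is about 16% unadjusted. With no link between infrastructure and behaviour (0.5/0.5), the unadjusted rate is nominal, 4.7%.

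**Step 6: what the contextual half of the same table would show.** Testing infrastructure by the same ANOVA at 200 respondents flags it in about 96% of simulated surveys at OR 3 and about 100% at OR 6.

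**The case against.** The strongest reply is Step 6. The plan compares contextual factors as well, so wherever access produces a false psychosocial signal, the access difference will nearly always appear in the same table. Investigators who read the whole table would be warned. This stands, and it limits the harm. It does not answer the question, though: seeing that both differ does not tell the reader whether the psychosocial difference survives at equal access.

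Second, the work is exploratory and the article condenses a fuller plan, which may contain a regression. That possibility is why this is a request to state or add a model and not a claim that none exists. The point rests on the method that the article does name.

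Third, infrastructure may partly be a consequence of norms or commitment, as when a household builds a latrine because it values one. Adjustment would then remove part of a real effect. This is a fair objection to replacing the ANOVA, and the reason to show both results.

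Two stronger readings are tempting, and the document supports neither. A reader might infer that regions are pooled and therefore uncontrolled; the survey is sized by region and the text is silent on pooling, so the rates above stay at one region's 200 respondents. A reader might also infer that the ANOVA decides which technique is used; the article says only that the data inform potential techniques.

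**Conclusion.** The concern holds in a limited form. As named, the RANAS analysis is an unadjusted comparison and cannot separate a psychosocial factor from access to infrastructure; nothing else in the article does so for doer status. The bias has no size that the document can supply. At 200 respondents and with no psychosocial effect, the assumed inputs of the main illustration give false-positive rates of about 8% to 60%, against about 5% with infrastructure in the model. Those rates depend on infrastructure being linked to both the behaviour and the score; without a link to the behaviour there is no inflation. The consequence is a risk of misreading a structural barrier as a psychosocial one, in an exploratory component whose contextual results would usually give some warning. It should be corrected in the analysis wording and does not call the survey into question.

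**What to change.** Keep the ANOVA table as description. For each target behaviour, add a logistic model of doer status on the psychosocial factors, including a short, named set of the infrastructure and socio-economic items already collected, and site. Allow for the two respondents per household with a household random effect or cluster-robust standard errors. State whether sites are pooled.

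Report unadjusted and adjusted estimates side by side, because infrastructure may lie partly on the pathway. Call a factor a psychosocial driver only with the adjusted result in view; otherwise describe it as an unadjusted association.

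The cost is analysis time and wording. The data are collected and the record linkage is already planned. Intervals will be wider, and correlated psychosocial and contextual items may make estimates unstable with at most 200 paired respondents per region, so the covariate set should be kept small.
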